### Sample size

Based on a review of previous research literature and the sample size calculation formula Health Statistics (14), equivalence tests were used to estimate the sample size. After 2 weeks of treatment, the NIHSS score for 63 patients in the observation group (conventional drug + acupuncture) was 7.53 ± 4.04, while the score for 63 patients in the control group (conventional drug only) was 12.61 ± 5.86. To calculate the sample size using an independent samples t-test, we need: effect size (Cohen’s d), significance level (*α*), power (1-*β*), and degrees of freedom (df). Cohen’s d is used to calculate the effect size, and the formula for Cohen’s d is: 
$d=\frac{M1-M2}{{SD}_{\mathrm{pooled}}}$
. For the observation group (conventional medication + electroacupuncture treatment): mean M1 = 7.53, standard deviation SD1 = 4.04, and for the control group (conventional medication): mean M2 = 12.61, standard deviation SD2 = 5.86. The pooled standard deviation (SDpooled) is known to be 5.62. Substituting into the formula, we obtain d ≈ −0.9, which represents a large effect size. When calculating the sample size using power analysis, the effect size d = 0.9, the significance level is typically set at *α* = 0.05, and the power 1 − *β* = 0.9. The formula for the independent samples t-test is: 
$n=\frac{2{\left(\upsilon_{\alpha }+\upsilon_{\beta }\right)}^{2}\sigma^{2}}{\delta^{2}}$
. With α = 0.05, β = 0.1, and a bilateral test, u₀.₀₅ = 1.96, u₀.₁ = 1.28, it was assumed that the control and treatment groups had equal therapeutic effects, with a combined 
$s=\sqrt{\frac{\left(n_{1}-1\right)s_{1}^{2}+\left(n_{2}-1\right)s_{2}^{2}+\frac{n_{1}n_{2}}{n_{1}+n_{2}}{\left({\bar{x}}_{1}-{\bar{x}}_{2}\right)}^{2}}{n_{1}+n_{2}-1}}$
 standard deviation of 
σ=5.62
. The mean difference between the two groups was substituted into the formula 
$n=\frac{2{\left(1.96+1.28\right)}^{2}\times 5.62^{2}}{{\left(12.61-7.53\right)}^{2}}=25.7\approx 26$
, resulting in a sample size of 26 patients for each group, resulting in a total of 52 patients across both groups (15). Based on the Guiding Principles for Clinical Research of New Chinese Medicines, and accounting for a 20% dropout and follow-up rate, a total of 66 patients should be included.:33 patients in the control group (basic treatment) and 33 patients in the treatment group (basic treatment + acupuncture) (16).

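### The SD of 5.62 in the sample-size calculation is not a pooled SD, because it contains the treatment effect, and a superiority calculation is labelled as equivalence

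*Protocol article*

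**What the plan says.** The Sample size section of the protocol article takes its inputs from one earlier study at two weeks: "the NIHSS score for 63 patients in the observation group (conventional drug + acupuncture) was 7.53 ± 4.04", and "the score for 63 patients in the control group (conventional drug only) was 12.61 ± 5.86". It defines Cohen's d as the mean difference divided by SDpooled, and then says: "The pooled standard deviation (SDpooled) is known to be 5.62". From this it obtains d of about 0.9 in absolute value. With two-sided alpha 0.05 and power 0.90 it reaches 25.7, rounded to 26 per arm. A 20% allowance for dropout brings the total to 66.

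On the hypothesis, the section opens by saying that "equivalence tests were used to estimate the sample size". Where it introduces the combined SD it adds that "it was assumed that the control and treatment groups had equal therapeutic effects". The same paragraph also says "To calculate the sample size using an independent samples t-test, we need" and "With α = 0.05, β = 0.1, and a bilateral test", and "The mean difference between the two groups was substituted into the formula", that is, 12.61 − 7.53.

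**The concern.** There are two separate faults.

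**The SD.** In Cohen's d and in the two-sample formula, σ is the spread of patients within an arm. The printed formula for the combined SD adds n₁n₂/(n₁+n₂) times the squared mean difference and divides by n₁+n₂−1. That is the total SD of both arms merged, so the treatment effect itself inflates it. With equal arms, a pooled SD is the root mean square of the two arm SDs, so 4.04 and 5.86 cannot give 5.62. The published SD, d, n per arm and power all depend on this input.

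**The hypothesis.** An equivalence calculation needs a margin, and none is given. Equal effects and a 5.08-point difference cannot both be the planning assumption. The stated aim, in the Abstract and in the Discussion, is that acupuncture lowers NIHSS scores, which is a superiority aim. If the equivalence label stays, it invites a reader to take a non-significant result as evidence of equivalence, which this design cannot provide.

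**Working it through.** **Inputs (Sample size section).** n₁ = n₂ = 63; means 7.53 and 12.61; SDs 4.04 and 5.86; difference δ = 12.61 − 7.53 = 5.08; two-sided alpha 0.05 (u = 1.96); beta 0.1 (u = 1.28); dropout 20%.

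**1. Reproduce the plan's figures.**
- Within-group sums of squares: 62 × 4.04² + 62 × 5.86² = 1011.9 + 2129.1 = 3141.0.
- Between-group term: 63 × 63/126 × 5.08² = 31.5 × 25.81 = 812.9.
- Plan's combined SD: √[(3141.0 + 812.9)/125] = √31.63 = 5.624 (stated 5.62).
- d = 5.08/5.62 = 0.904 (stated 0.9).
- n = 2 × (1.96 + 1.28)² × 5.62²/5.08² = 25.7, so 26 per arm (as stated).
- 26/0.8 = 32.5, so 33 per arm and 66 in total (as stated).

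The arithmetic is consistent. The fault is in the SD that enters it.

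**2. Use the within-group pooled SD.**
- SD = √[3141.0/(63 + 63 − 2)] = √25.33 = 5.033.
- d = 5.08/5.033 = 1.009.
- n = 2 × 3.24² × 5.033²/5.08² = 20.6, so 21 per arm by the plan's formula. The noncentral t distribution gives 22.

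The gap between 5.624 and 5.033 comes from the between-group term, 812.9 of a total of 3953.9, or about 21%, together with the change of divisor from 125 to 124.

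**3. Power with SD 5.033, two-sided alpha 0.05, unadjusted (noncentral t).**

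| Evaluable per arm | True difference | Power |
|---|---|---|
| 26 | 5.08 | 94.6% |
| 33 | 5.08 | 98.1% |
| 26 | 4 | 80% |
| 26 | 3 | 56% |

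The normal approximation gives 95.3% for the first row. With 26 per arm, the difference detectable with 90% power is about 4.6 points.

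**4. Power if 5.62 is kept.** With 26 per arm, the normal approximation gives 90.3%. The t-test gives 89%, and 27 per arm would be needed to reach 90%. This gap reflects only the choice of approximation and is minor.

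**5. Hypothesis wording.** An equivalence calculation tests whether the difference lies inside a stated margin. The formula used here has no margin. It divides by the square of the full observed difference and uses 1.96 for a two-sided test, which makes it a calculation for detecting a difference. The Data monitoring and statistical analysis section likewise reads p < 0.05 as showing a difference.

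**The case against.** The strongest reply is that nothing in the design changes. The merged SD is too large, so the sample size errs on the safe side, and the 90% target is exceeded under the cited data. Alpha, the 5.08-point difference and the dropout allowance do not depend on the SD, and the formula is printed openly. This is all correct, and it limits the point to a correction of the paragraph.

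A second reply is that 5.03 is not guaranteed for this trial either. The source SDs are unequal; if the control SD of 5.86 applied in both arms, 26 per arm would give about 86.5% power. A planning SD of 5.62 is therefore not implausible. That stands as an argument for caution, but it is not the argument the plan makes. The plan calls 5.62 the pooled SD of the cited data, and it is not.

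A third reply is that the equal-effects phrase may be a clumsy statement of the null hypothesis under which the arms were merged, and that the rest of the article reads as superiority. That may be how the wording arose. It does not justify the SD, because the formula is evaluated at the alternative, with δ = 5.08, and there σ must be the within-arm SD. The risk that a null result is misread as equivalence is a matter of judgement, since no equivalence analysis is planned. The contradiction in the text remains. Showing power at smaller differences goes beyond correcting an error, but it is useful because 5.08 comes from a single study.

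**Conclusion.** The concern holds on both counts. The value called pooled is the total SD of the merged arms: 5.62 in place of 5.03. It follows that d should be 1.01 rather than 0.9, and n should be 21 per arm (22 by the t-test) rather than 26. Power at 5.08 points is about 95% with 26 evaluable per arm and about 98% with all 33, against the stated 90%. These figures assume that the source study's means and SDs carry over to this trial, and that a two-sided, unadjusted 5% test is used on a single comparison. The error is conservative, so the trial is not underpowered because of it. The equivalence and equal-effects wording changes no number, but it misstates the hypothesis and contradicts the calculation in the same paragraph.

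**What to change.** Rewrite the sample-size paragraph as follows:
- State a two-sided superiority test, and delete the references to equivalence tests and to equal therapeutic effects.
- Replace the combined-SD formula with the within-group pooled formula, 5.62 with 5.03, and d = 0.9 with d = 1.01.
- Report that the corrected formula needs 21 per arm (22 by the t-test). Keep 66 patients as a deliberately conservative choice, and give power at 5.08 points as about 95% with 26 evaluable per arm and about 98% with 33.
- Preferably add power at smaller differences, for example 80% at 4 points and 56% at 3 points with 26 per arm, unadjusted, so that the reliance on 5.08 is visible.

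The cost is rewording one paragraph. Enrolment does not change.

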### Data monitoring and statistical analysis

To minimize measurement bias arising from multiple evaluators, clinical indicator assessments and laboratory tests for each patient before, during, and after treatment will be conducted by the same specialized physician whenever possible. The physician evaluating the laboratory indicators will be blinded to the group assignments and treatment. To avoid missing or incorrect data, clinical and laboratory indicator evaluations will be conducted according to preset time points and entered into the electronic database promptly.

Data management and analysis will be performed using IBM SPSS Statistics Version 26 (IBM SPSS Inc., Chicago, United States). The principles of data processing are as follows: measurement data will be expressed as mean ± standard deviation (
$\bar{x}$
± S); if count data are normally distributed, the chi-square test will be used; if data in the two groups are normally distributed, t-test, repeated-measures analysis of variance (ANOVA), and multivariate linear regression will be used for comparative analyses; if count data are not normally distributed, the Mann–Whitney U test will be used; *p* < 0.05 will indicate statistically significant differences.

We will use the last observation carried forward (LOCF) method, which replaces missing data points with the patient’s last observed value. In order to provide a more comprehensive assessment of the treatment effects in this study, we will conduct both an intention-to-treat (ITT) analysis and a per-protocol (PP) analysis.

We will implement the Bonferroni correction during statistical analysis to rigorously control Type I error rates, thereby ensuring methodological stringency in accordance with your recommendation.

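### The 90% power is derived for 26 completers per arm; the power of the promised ITT analysis with LOCF is not given and may, but need not, be lower

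*Protocol article*

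**What the plan says.** The Sample size section sets the error rates ("With α = 0.05, β = 0.1, and a bilateral test") and takes its inputs from an earlier study: "mean M1 = 7.53, standard deviation SD1 = 4.04" for acupuncture and "mean M2 = 12.61, standard deviation SD2 = 5.86" for control, both after 2 weeks of treatment. It uses an SD of 5.62 and arrives at 26 per arm, 52 in total. It then enlarges the trial: "accounting for a 20% dropout and follow-up rate, a total of 66 patients should be included", that is, 33 per arm.

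The section on data monitoring and statistical analysis says "We will use the last observation carried forward (LOCF) method" for missing data, and also "we will conduct both an intention-to-treat (ITT) analysis and a per-protocol (PP) analysis". Outcome measurement schedules the NIHSS on Days 1, 5 and 10. Termination criteria lists events such as ICU transfer, serious adverse reactions, intolerance to electroacupuncture and withdrawal, and says that patients who meet them leave the study. Nothing in the article says that their NIHSS is still taken afterwards.

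**The concern.** Dividing by 0.8 makes sense if the lost patients leave the analysis and 26 per arm remain, each showing the full expected difference. That describes a completer analysis. An ITT analysis with LOCF works differently: nobody leaves, but a lost patient is represented by an earlier score. A Day 1 score holds no treatment effect, and a Day 5 score holds whatever part has appeared by then. The number analysed goes up and the expected difference goes down, and the protocol does not weigh one against the other.

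The ITT analysis is the one that keeps the randomised comparison intact. If its power is below the stated 90%, the trial has a larger chance than its readers expect of missing a true effect in that analysis. Carrying early scores forward can also bias the estimated difference, and that matters whatever the power is.

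**Working it through.** **Inputs from the Sample size section.** Means 7.53 and 12.61 (difference 5.08); SDs 4.04 and 5.86 with 63 patients per group; SD used 5.62; two-sided 0.05; power 0.90; loss 20%.

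**Reproducing the plan's figures.**
- n = 2 × (1.96 + 1.28)² × 5.62² / 5.08² = 25.70, so 26 per arm.
- 26 / 0.8 = 32.5, so 33 per arm and 66 in total.
- Power with 26 per arm at difference 5.08 and SD 5.62 is 90.3% by the normal approximation and 89.2% by the noncentral t.

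So the 90% is the power for 26 completers per arm with the full effect.

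**ITT with LOCF.** Let f be the average share of the full effect that a lost patient's carried score shows. The protocol does not give f. With 20% lost before Day 10 in both arms, the expected difference is 5.08 × (0.8 + 0.2f), with 33 analysed per arm.

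Three cases follow. They assume that a Day 5 score shows half the effect. The first two power columns use the noncentral t. The last two come from simulations of 40,000 trials, which add the spread from mixing early and late scores. They assume a baseline NIHSS mean of 13 to 15 and SD 5, which the documents do not give.

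| Score carried by lost patients | f | Expected difference | SD 5.62 | SD 5.03 | SD 5.62, added spread | Arm SDs 4.04/5.86, added spread |
|---|---|---|---|---|---|---|
| All Day 1 | 0 | 4.06 | 82.5% | 89.8% | 78-81% | 83-87% |
| Half Day 1, half Day 5 | 0.25 | 4.32 | 86.7% | 93.0% | 84-87% | 90-91% |
| All Day 5 | 0.5 | 4.57 | 90.2% | 95.3% | 89-90% | about 95% |

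If carried scores showed the full effect (f = 1), power with SD 5.62 would be 95.1%. With that SD and no added spread, ITT power equals 90% at f of about 0.41 (normal approximation) or 0.48 (noncentral t).

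**Why SD 5.03 appears.** The plan's formula for 5.62 includes the between-group difference: √[(62 × 4.04² + 62 × 5.86² + 31.5 × 5.08²) / 125] = 5.62. This is a total SD. The within-group SD is √[(4.04² + 5.86²) / 2] = 5.03. With 5.03, 26 completers per arm have 95.3% power (normal approximation; 94.6% by the noncentral t).

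**If only 10% are lost before Day 10.** With SD 5.62 the same three cases give 90.2% to 93.0% by the noncentral t, and about 88% to 93% with the added spread.

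**The case against.** A reader might infer that the arithmetic is wrong, or that the ITT analysis is shown to be underpowered. The documents support neither.

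- Every stated number reproduces, and the protocol nowhere says that the 90% belongs to the ITT analysis.
- ITT keeps seven more patients per arm (33 against 26), which offsets part or all of the dilution. If all losses come after Day 5 and half the effect is present by then, power is about 90%.
- The SD of 5.62 is larger than the within-group SD, which gives a cushion. With 5.03, even the all-Day-1 case is close to 90% before any added spread.
- The 20% is worded to cover dropout and follow-up together, and the protocol has visits 1 and 3 months after discharge. Some of that loss may fall after Day 10 and leave the NIHSS untouched. The patients are inpatients on a 10-day course.

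All of this stands, and it rules out a claim of a fixed shortfall. It does not turn the 90% into the power of the ITT analysis, because that power depends on f and on when patients are lost, and the protocol gives neither.

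A second tempting reading is that the plan fails because it does not name ITT or PP as decisive. That choice is commonly made in the full protocol or analysis plan, which is not shown, so it is not part of this point.

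**Conclusion.** The sample size and the promised ITT analysis rest on different sets of patients and different expected differences. The 90% holds for 26 completers per arm at 5.08 points; for ITT with LOCF no power was derived.

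On the plan's own SD, with the full 20% lost before Day 10 equally in both arms, ITT power runs from about 78-83% (all Day 1 scores) through 84-87% (half Day 5 at half the effect) to about 90% (all Day 5 at half the effect). With the stated arm SDs it is about 83-95%. The ITT analysis may therefore fall below 90%, but need not. The lower ends depend on an assumed baseline distribution, and every figure depends on the assumed effect share.

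This is a modest point. It is worth acting on because the remedy is cheap and also limits the bias that carried-forward scores can bring.

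**What to change.** 1. In Termination criteria and in the analysis section, state that patients who stop the intervention but do not withdraw consent still have the scheduled Day 5 and Day 10 NIHSS taken, and that these scores are analysed in the randomised arm. Use LOCF only where no score can be obtained. The rules for stopping treatment stay as they are; only data collection afterwards is affected.
2. In the Sample size section, say that the 90% refers to 26 completers per arm. Give ITT power as a range, together with the assumption about when patients are lost and how much of the effect their last score shows.

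The cost is a few sentences and a few extra ratings, at visits already scheduled, in patients who have stopped treatment. Patients who withdraw consent are not covered, so some LOCF will remain. No extra patients are needed.

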### Random allocation

A total of 66 patients were enrolled using simple randomization with a random number table and randomly assigned to the treatment group and the control group. The group assignments and treatment protocols were placed in opaque envelopes and kept by the attending physicians and acupuncture therapists, who administered the treatment according to the instructions in the envelopes.

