**Methods:**

Sixty-six patients with acute ischemic stroke will be randomly assigned 1:1 to control (conventional basal therapy, *n* = 33) and acupuncture (conventional standard stroke care + acupuncture, *n* = 33) groups for 10 days of intervention. The primary outcome is NIHSS score. The secondary outcomes: BMI and mRS scores, the level of TNF-A and IL-1B in serum, vascular endothelial growth factor (VEGF), Endocan ES, CD14+ and CD14- levels of peripheral blood mononuclear cells.

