### Exclusion criteria

Patients who meet any of the following criteria will be excluded from the study:

(1) Transient ischemic attacks, subarachnoid hemorrhage, cerebral hemorrhage, or other similar conditions;(2) Patients requiring arterial or venous thrombolysis or thrombectomy based on their condition;(3) Individuals suffering from immune-related diseases, such as acute or chronic infections, tumors, and blood disorders, or who have severe organ dysfunction;(4) Individuals with severe cardiovascular dysfunction, upper gastrointestinal bleeding, intolerance to electroacupuncture, or those with pacemakers or stents;(5) Pregnant, pre-pregnant, or lactating individuals;(6) Family members or patients who exhibit poor initiative or lack cooperation;(7) Participants who have participated in other clinical trials within 1 month prior to this study.

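### The clinicians who treat the patients hold the allocation envelopes, so the stated procedure permits foreknowledge of assignments; separately, simple randomisation cannot guarantee the stated 33:33 split

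*Protocol article*

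**What the plan says.** Under Random allocation, the protocol article states that 66 patients were "enrolled using simple randomization with a random number table". The assignments, together with the treatment protocols, were "placed in opaque envelopes and kept by the attending physicians and acupuncture therapists". The same section adds that these staff then treated each patient as the envelope directed. The custodians and the treating staff are therefore the same people. The article names no custodian independent of treatment and no control on when an envelope may be opened.

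The arm sizes are given as fixed numbers. The Methods paragraph of the Abstract says "Sixty-six patients with acute ischemic stroke will be randomly assigned 1:1 to control" and acupuncture, with n = 33 in each. The Sample size section ends with "33 patients in the control group (basic treatment) and 33 patients in the treatment group", and the Interventions section repeats 33 for each arm. No blocking or other restriction is mentioned.

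One of the exclusion criteria reads "Family members or patients who exhibit poor initiative or lack cooperation".

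The Blinding section says that outcome assessors, including the NIHSS raters, and statisticians are fully blinded, and that grouping is concealed from laboratory staff. Treating staff are not listed as blinded, which is unavoidable with this intervention.

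**The concern.** Allocation concealment means that whoever decides on a patient's entry cannot know the next assignment. An opaque envelope gives no protection against the person who keeps it unless something else controls when it is opened. Here the keepers are clinicians who know the arm of every patient they treat. If they also screen or influence entry, they could let the next assignment affect whether a borderline patient is included. The cooperation criterion is a judgement that could carry such a decision.

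What is at stake is the comparability of the arms at baseline. The inclusion criteria admit NIHSS scores from 3 to 20, and the primary outcome is the NIHSS, so even modest steering by severity or expected cooperation would feed into the result. Adjustment for baseline NIHSS would correct only what was measured. With 33 per arm, a few steered patients matter.

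The conflict between simple randomisation and 33:33 is a lesser matter. Either the method or the arm sizes are loosely described. If the list was in fact restricted or topped up to reach equal numbers, some late assignments could be worked out by anyone keeping a count.

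**Working it through.** **Custody.** No arithmetic applies; the sections are set side by side.
- Random allocation: treating staff keep the envelopes and treat according to their contents.
- Exclusion criteria: at least one criterion is a subjective judgement.
- Blinding: protection is given to raters, statisticians and laboratory staff. That protects measurement and analysis after allocation, and has no bearing on who enters which arm.
- Who enrols, and who applies the exclusion criteria: not stated.

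The procedure therefore permits foreknowledge, but the text does not show that it happens.

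**The plan's own sample size.** Inputs from the Sample size section: difference 12.61 − 7.53 = 5.08, SD 5.62, two-sided α = 0.05, power 0.90, dropout 20%.
- n = 2 × (1.96 + 1.28)² × 5.62² / 5.08² = 25.7, rounded to 26 per arm.
- 26 / 0.8 = 32.5, rounded to 33 per arm, 66 in total.

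Both figures reproduce.

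**Arm sizes under simple randomisation.** The size of one arm is Binomial(66, 0.5), with SD √(66 × 0.25) = 4.06.
- P(exactly 33:33) = C(66,33) / 2⁶⁶ = 0.098, so some other split occurs with probability 0.902.
- P(28:38 or more unequal) = 0.268.
- P(26:40 or more unequal) = 0.109.
- P(smaller arm below 26) = 0.064.

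**How many final assignments become known.** This depends on how, or whether, equal arms are reached, which the article does not say.

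| Mechanism (assumed) | Mean number of forced final assignments | P(10 or more) |
|---|---|---|
| True simple randomisation, arms left as they fall | 0 | 0 |
| Random allocation rule (33 and 33 in random order) | 2 × 33 / 34 = 1.9 | 2 × C(56,23) / C(66,33) = 0.001 |
| Simple randomisation, arm closed on reaching 33 | 66 × 0.0978 = 6.5 | 2 × P(Bin(56, 0.5) ≤ 23) = 0.229 |

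The last mean follows because, if allocation had continued by coin toss after closure, the fuller arm would on average have exceeded 33 by half the forced tail. The mean tail is therefore twice E|X − 33|, and for Binomial(66, 0.5) E|X − 33| = 33 × C(66,33) / 2⁶⁶ = 3.23.

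**Power under imbalance.** Each arm is reduced by 20% dropout. Power = Φ(5.08 / SE − 1.96), with SE = 5.62 × √(1/(0.8a) + 1/(0.8b)).

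| Split a:b | SE | Power |
|---|---|---|
| 33:33 | 1.547 | 0.907 |
| 29:37 | 1.558 | 0.903 |
| 26:40 | 1.583 | 0.894 |
| 25:41 | 1.594 | 0.890 |

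Going from 33:33 to 25:41 costs under two percentage points.

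**The case against.** The strongest reply is that foreknowledge is inferred. The article does not say that the envelope holders screen or enrol. The envelopes are opaque, and the text could describe instructions passed to treating staff after assignment. Sealing, numbering and time of opening are details that a journal article often leaves to the full protocol. All of this is fair, and the absence of those words is not relied on here. It does not remove the point: the article states positively who keeps the assignments, and that party is unblinded and delivers the intervention.

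A second reply is that the NIHSS raters and statisticians are blinded. That lowers the risk of measurement bias and should be acknowledged, but it acts after allocation.

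On 33:33, a reader might infer that simple randomisation cannot produce the split, that the list must therefore have been cut off at 33, and that about 6.5 assignments were known in advance. The documents do not support this. An exact split has a 9.8% chance, closing an arm is nowhere mentioned, and shuffling 33 and 33 also gives equal arms with a much shorter forced tail. The stated 33 can also be read as a target, since it is the expected arm size. True simple randomisation is the least predictable method, so it adds nothing to the custody problem. A forced tail also matters only if someone keeps count. This half is accordingly a matter of consistent description.

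**Conclusion.** The custody point stands. The article assigns the allocation envelopes to the staff who treat, names no independent holder, and so describes a procedure that permits foreknowledge of assignments. That is a poor rule as stated, not a detail lost in condensation. A reader might infer that selection has occurred or will occur; the documents do not show this, because they do not say who enrols or who applies the exclusion criteria. The size of any resulting bias cannot be calculated from the article.

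The secondary point stands in a limited form. Simple randomisation cannot guarantee 33:33 (probability 0.098). The average number of known final assignments ranges from 0 to about 6.5, depending on a mechanism that the article does not state. Imbalance has little effect on power, given the plan's own difference, SD and 20% dropout in each arm.

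**What to change.** 1. Delete the clause that gives the attending physicians and acupuncture therapists custody of the envelopes. Name an existing member of staff who does not enrol, treat or rate patients (for example a data manager) to hold the sequence.
2. State that each assignment is released only after consent, eligibility and the Day 1 NIHSS have been recorded.
3. Reconcile the method with the arm sizes. Either keep simple randomisation and write about 33 per arm in the Abstract, Sample size and Interventions sections, or state the restricted method used. If that is permuted blocks, the sizes should vary and be undisclosed to recruiting and treating staff, because clinicians at a single site who know past assignments can otherwise guess some of the next ones.
4. The Random allocation section is in the past tense, so enrolment may have begun. If so, apply the new custody to the remaining patients and report the earlier procedure as a limitation.

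The cost is a change of protocol wording and a transfer of the envelopes. Keeping simple randomisation needs no new list. The small continuing burden is contact with the custodian at each enrolment. No treatment, outcome or sample size changes.
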